## Abstract

**Clinical trial registration:**

clinicaltrials.gov, identifier NCT06023407.

## Highlights

This study is designed to evaluate the metabolic effects of a 10-week Heat therapy (HT) intervention in older adults.Main whole-body outcomes are HbA1c, insulin sensitivity index, and continuous glucose monitoring.Brain glucose metabolism measured by FDG-PET imaging will be evaluated as a secondary outcome.Vascular measures such as blood pressure and effects on AD-relevant blood biomarkers will also be assessed.

## Introduction

1

Alzheimer’s Disease (AD) is the leading form of dementia and it is estimated that AD could affect approximately 15 million people by 2050 (1). The incidence of prediabetes and diabetes increase substantially with age, which is important because there is accumulating evidence that metabolic and vascular diseases increase risk for Alzheimer’s Disease (AD).

Heat Therapy (HT), primarily via hot water immersion that raises core body temperature, has been independently shown to improve risk factors for cardiometabolic disease. Long term HT (8–10 weeks) results in improvements in blood glucose regulation, insulin resistance, inflammation, and blood pressure in both young, healthy individuals and in obese populations (2–5). Importantly, improvements in these modifiable cardiometabolic outcomes could lower risk for AD (6–10). It is well established that fasting glucose levels increase with aging, and that impaired glucose metabolism is a risk factor for AD (11).

Prior work suggests that peripheral glucose levels have an inverse relationship with brain glucose metabolism (12). Brain hypometabolism, a marker of reduced energy metabolism, is also a reliable and early diagnostic biomarker of AD (12, 13). In cognitively healthy older adults, peripheral hyperglycemia is associated with decreased cerebral glucose metabolism in several brain regions on Flurodeoxyglucose positron emission tomography (FDG-PET) including the precuneus, posterior cingulate, and parietal regions (14–17). These regions are core components of a set of connections called the Default Mode Network, which are regions that exhibit some of the highest metabolic rates in the brain (18, 19), hypo-metabolism in AD (12, 13), and are among the first to accumulate amyloid (20). This suggests that improving peripheral hyperglycemia may be particularly important for brain health in individuals with elevated glucose levels.

Here, we describe the clinical trial protocol of the Feasibility of Improving Glycemia to prevent AD (FIGHT-AD) study. This trial compares the effects of hot and warm water immersion on blood and brain glucose metabolism in cognitively healthy older adults with metabolic syndrome following a 10-week intervention. Hot water immersion has a more robust effect on core temperature compared with other whole body heating modalities (i.e., traditional sauna and far-infrared sauna approaches) (21), potentially affording the greatest physiological responses in our study population. Individuals will undergo up to 30 sessions of hot (40.5 °C, *n* = 30) or warm (36 °C, *n* = 30) water immersion to assess the effect of temperature on the changes in blood and brain glucose metabolism (pre to post). We hypothesize that 10 weeks of thrice weekly HT will lower hemoglobin A1c (HbA1c) values and improve insulin sensitivity index outcomes. Additionally, we hypothesize that individuals will improve (increase) global cerebral glucose metabolism following 10 weeks of HT. We will also explore effects on other outcome measures such as blood pressure, blood AD biomarkers, and brain blood flow.

## Materials and equipment

2

Whole body and regional fat mass, fat-free mass, percent body fat, and bone mineral density will be assessed using a dual energy x-ray absorptiometry scan (DEXA) scan (GE Lunar iDXA).

Heart rate and blood pressure will be captured with an automatic blood pressure monitor (Connex® Spot Monitor, Welch Allyn, Inc). An IV catheter will be placed for blood collection and assessment of a Glucose Tolerance Test. Participants will be instructed to consume a 75 g beverage (TRUTOL® 75, Fisher Diagnostics) at the start of the test. Flurodeoxyglucose (FDG) is administered with FDG-PET, performed with a GE Discovery ST-16 PET/CT scanner.

Magnetic Resonance Imaging (MRI) will be performed with a Siemens 3.0 Tesla Skyra scanner. G6 Pro Continuous Glucose Monitoring (CGM) will be utilized (Dexcom, San Diego, CA). Core temperature will be assessed and recorded using eCelsius Performance Pills and ePerformance Manager software (BodyCap, Hérouville-Saint-Clair, Normandy, France). Urine specific gravity to confirm euhydration will be determined with a refractometer (Fisherbrand™ Handheld Analog Clinical Refractometer, Thermo Fisher Scientific, Waltham, MA). Hot water and thermoneutral immersion will be performed in two commercial hot tubs (Marquis Rendezvous and Freeflow Tristar Spa). Whole blood will be analyzed at baseline for HbA1c using the DCA Vantage Analyzer (Siemens, Tarrytown, NY) and for lipid analysis using the Cholestech LDX Lipid Profile Test Cassette (Abbott, San Diego, CA). TNF, IL-6: Cytokine 4-Plex A (C4PA) Advantage PLUS, Neuro 2 Plex B assay (N2PB) will be measured using the Simoa HD-X (Quanterix, Billerica, MA) and phosphorylated tau 217 and amyloid beta 42 on the Lumipulse G1200 (Fujirebio).

## Methods

3

### Trial design

3.1

FIGHT-AD is a two-arm, prospectively enrolling randomized controlled trial that compares the effects of thrice weekly HT in water immersion for 10 consecutive weeks on glucose metabolism in warm (*n* = 30) and hot (*n* = 30) water. Participants will complete telephone cognitive testing and clinical evaluation to screen for any cognitive impairment. After screening, informed consent will be obtained and participants will be enrolled into the study. Cognitively healthy older adults who meet the criteria for metabolic syndrome will be enrolled and complete (1) a fasting blood draw; (2) an Oral glucose tolerance test (OGTT); and (3) CGM, MRI and an FGD-PET scan. Assessments will be repeated following 10 weeks of HT. Participants will undergo 30 sessions of HT in 40.5 °C water or 36 °C water to assess the effect of temperature on changes in blood and brain glucose metabolism. The flow of the study is illustrated in Figure 1.

**Figure 1 fig1:**

Study flow for FIGHT-AD. Pre-screening by the KU ADRC recruitment division will result in pass-offs to the study team. Participants will be consented prior to cognitive evaluation to screen out cognitive impairment. Pre-treatment baseline evaluations will be performed at 3 in-person visits (OGTT, MRI, PET). CGM will also be placed at visit 3. After completing all 3 pre-treatment evaluation visits and meeting inclusion criteria, participants will be randomized to intervention groups (Hot water or Warm water). Participants will attend intervention or thermoneutral visits with study team at treatment evaluations and complete the study.

#### Trial registration and outcome measures

3.1.1

The initial IRB approval for the FIGHT-AD study occurred on March 3, 2023. The trial was registered on clinicaltrials.gov on August 28, 2023 (NCT06023407). Upon completion of the trial, results will be made available on clinicaltrials.gov. Upon primary analysis and publication of the study outcomes, data will be made publicly available to other researchers. The primary outcomes are changes in glycated hemoglobin (HbA1c) and insulin sensitivity index (ISI). The secondary outcome measure is change in cerebral glucose metabolism, quantified as [18F] FDG global standardized uptake value ratio (SUVR) assessed pre- vs. post-HT. Exploratory outcome measures include the effects of HT on blood pressure, inflammation (CRP, TNF, IL-6, JNK and IKK) and AD biomarkers (Amyloid/Tau/Neurodegeneration measures), and neuroimaging measures of vascular function.

### Recruitment and participants and ethics approval

3.2

Participants are recruited and prescreened through the University of Kansas Alzheimer’s Disease Research Center. All study visits occur at the University of Kansas Medical Center. A trained study staff member obtains informed consent from all participants through a signed consent form on the day of their first visit. This study was approved by the Institutional Review Board (IRB) at the University of Kansas Medical Center (IRB: STUDY00147285). Any modifications to the research protocol, should they be made, will be reviewed and approved by the IRB. All procedures are performed in accordance with the Declaration of Helsinki. All reasonable efforts are made to ensure data and participant privacy and confidentiality. Upon completion of the study, we will provide a letter to participants informing them of the study findings and where they can access the resulting publication.

Participants complete an initial screening process to determine their eligibility. Eligible participants are 65 years and older and have been evaluated to be cognitively healthy (Clinical Dementia Rating (CDR) = 0) using a remote CDR and single clinician diagnosis (22). Individuals must be on stable medication doses, and female participants must be post-menopausal to participate. Furthermore, participants must have an existing diagnosis of either prediabetes or type 2 diabetes (T2D). If a participant does not have prediabetes or T2D, participants must have 2 out of the 3 following: BMI > 30, Hypertension, or Dyslipidemia. Individuals with type 2 diabetes treated with non-insulin pharmacologic agents were eligible for inclusion provided medication doses were stable for at least one month prior to enrollment; insulin-dependent diabetes mellitus was excluded. A complete list of inclusion and exclusion criteria are provided in Table 1.

**Table 1 tab1:** Inclusion and exclusion criteria used during pre-screening process.

Inclusion criteria	Exclusion criteria
Age 65 and older Stable medication doses (>1 month) Post-menopausal Clinical Dementia Rating (CDR) of 0 History of or current metabolic impairment (i.e., metabolic syndrome, pre-diabetes, Type 2 Diabetes, etc)	Excluded from or unable to complete an MRI scan. MRI compatible pacemakers will require cardiologist clearance prior to enrolling. ACSM Risk score stratification of “High” unless cleared by a physician prior to participation. Myocardial infarction or symptoms of coronary artery disease in the last 2 years. History of or current diagnosis of disorders with the potential to impair cognition (i.e., AD, Parkinson’s disease, stroke (defined as clinical episode w/ neuroimaging evidence in appropriate area to explain symptoms)). Insulin-dependent Diabetes Mellitus. Clinically significant chronic disease such as cancer, HIV, or acquired immunodeficiency syndrome. Clinically significant depressive symptoms that may impair cognition, use of psychoactive and investigational medications, and significant visual or auditory impairment. Orthopedic complications that would preclude individuals from safely entering a hot tub. Current or significant history of lower body wounds or diabetic ulcers Untreated hypothyroidism or diseases associated with heat intolerance (i.e., Graves disease, etc.). Contraindication for temperature pill ingestion (i.e., inflammatory bowel disease, diverticulitis or related). Participants may participate in other observational studies but cannot participate in other studies in which they receive an intervention.

MRI, Brain magnetic resonance imaging; ACSM, American College of Sports Medicine; AD, Alzheimer disease; HIV, Human immunodeficiency virus.

### Procedures

3.3

Overall study flow is shown in Figure 1 and list of procedures at each study visit is given in Table 2. First, participants are screened by phone and basic demographic information is collected. The American College of Sports Medicine Participation Health Screening was used to assess risk stratification. Participants who were characterized as “High Risk” were excluded unless a physician clearance was provided. Once deemed eligible, all subsequent screening procedures and in-person study visits are completed over the course of about 14 weeks. Participants are administered a neuropsychometric exam (National Alzheimer’s Coordinating Center Uniform Data Set telephone cognitive battery; T-Cog) by a trained psychometrician, as well as a telephone diagnostic assessment (Telephone CDR; T-CDR) by a trained clinician. Following participant consent, medical history and medication use information are collected via patient report. Pre-treatment assessment also includes a dual energy x-ray absorptiometry scan (DEXA) and OGTT. At the following visit, participants are administered FDG prior to the PET, to measure brain glucose metabolism. CGMs will be utilized to assess 24 h continuous glucose measures in a daily living environment. Each participant also completes a MRI scan.

**Table 2 tab2:** Procedures administered at each telephone or in-person study visit.

Assessment	Pre-screen	Visit 1	Visit 2	Visit 3	Intervention (10-weeks)	Visit 4	Visit 5	Visit 6
Demographics	X							
Medical history	X	X				X		
Medications	X	X				X		
Telephone CDR	X							
Telephone cognitive test	X							
Anthropometrics/Vitals		X			X	X		
DEXA		X				X		
Blood draws					X (Wk 4)	X		
Oral glucose tolerance test				X	X (after final treatment)			
Continuous glucose monitoring (7 days following visit)		X				X		
FDG-PET scan			X				X	
MRI				X				X
Randomization				X				
Heat or thermoneutral sessions					X			

CDR, Clinical dementia rating; DEXA, Dual energy X-ray absorptiometry; FDG-PET, (18)F-fluorodeoxyglucose positron emission tomography; MRI, Magnetic resonance imaging.

Following successful completion of baseline assessments, participants are randomized to receive treatment in hot or warm water temperature group. An allocation table was created by the unblinded study statistician working with the study team. Randomization is performed using the REDCap randomization module (23). Individuals are randomized 1:1 to intervention group according to the allocation table accounting for sex and age to ensure approximately equal representation among HT groups. At each subsequent study visit, participants complete 45 min of HT. Assessment of DEXA, GTT, FDG-PET, CGM and MRI are repeated after 10 weeks HT. Study staff who oversee therapy sessions will be unblinded to study group. All outcome assessors (psychometricians, nursing staff, neuroimaging technicians, etc) are blinded to participant intervention group. Study data is stored using REDCap software in a secure study database.

#### Visits 1 & 4

3.3.1

##### Dual energy X-ray absorption scan

3.3.1.1

The first and fourth assessment is scheduled in the morning following an overnight fast, with the latter (post-intervention visit) being scheduled at most 72 h after their last HT session. Following informed consent, information regarding demographics, and anthropometric data is collected. At each visit participants change into lightweight hospital gowns and are instructed to remove all metal objects (i.e., jewelry, hairpins, etc.) that may interfere with accuracy of the measurement. Participants remain in the supine position throughout the DEXA scan (GE Lunar iDXA). This provides data for whole body and regional fat mass, fat-free mass, percent body fat, and bone mineral density. The scanner is calibrated each day prior to use according to manufacturer guidelines (22).

##### Oral glucose tolerance test

3.3.1.2

Following the DEXA scan, heart rate and blood pressure are measured after 5 min of seated rest. Heart rate (HR) and Blood pressure (BP) are captured with an automatic blood pressure monitor (Connex® Spot Monitor, Welch Allyn, Inc). An IV catheter is placed for blood collection throughout the study visit and the baseline draw is collected. Participants are instructed to consume the 75 g beverage (TRUTOL® 75, Fisher Diagnostics) within 5 min and OGTT begins once the entire beverage has been consumed. Blood Draws 2, 3, 4 are collected at minutes 30, 60 and 120, respectively. Blood processing procedures are described in section 3.4.

#### Visits 2 & 5 FDG-PET scan

3.3.2

At the FDG-PET scan, participants arrive after having fasted approximately 8 h. Participants receive a single IV bolus of FDG approximately 30 min prior to the start of the scan. FDG-PET are performed with a GE Discovery ST-16 PET/CT scanner. The FDG-PET scan includes six, five-minute frames that are attenuation corrected and reconstructed into a single FDG-PET image. FDG-PET images will be analyzed using custom software written for Statistical Parametric Mapping (SPM12). For each participant, the FDG-PET images from both the pre- and post-HT condition will be co-registered to the participant’s pre-anatomical MRI image. *A priori* individualized, native space region of interest masks will be generated from the Computational Anatomy Toolbox (CAT12) for SPM. The FDG-PET images will be SUVR of the cerebellum.

#### Visits 3 & 6 brain magnetic resonance imaging (MRI) and continuous glucose monitoring (CGM)

3.3.3

Participants complete an MRI safety screening upon arrival to Hoglund Biomedical Imaging Center. Scans are performed with a Siemens 3.0 Tesla Skyra scanner. High-resolution T1 weighted images (MP-RAGE; 1 × 1 × 1 mm voxels; TR = 2,300, TE = 2.98, TI = 900, FOV 240 × 256, 1 mm slice thickness, flip angle 9 degrees) are acquired for detailed anatomical assessment and co-registration of the PET scans. In addition to structural measures, we also obtain measures of fluid attenuated inversion recovery (FLAIR; 0.9375 × 0.9375 × 5.0 mm voxels, TR = 9,000, TE = 91.0, FOV = 256 × 256, flip angle 150 degrees) cerebral blood flow (pcASL; pseudocontinuous, 3.125 × 3.125 × 2.5 mm voxels, TR = 4,300, TE = 22.42, FOV 672 × 672, flip angle 120 degrees), and cerebral oxygen extraction fraction (T2 -relaxation-under-spin-tagging; TRUST; 3.4375 × 3.4375x5mm voxels, TR = 3,000, TE = 7.1, FOV 64 × 64, flip angle 90degrees). G6 Pro Continuous Glucose Monitoring (Dexcom, San Diego, CA) will be utilized and worn for 7–10 days pre- and post-intervention.

### Heat therapy and thermoneutral control sessions

3.4

Participants will be scheduled for 30 sessions over 10 weeks of either hot water immersion (heat group) or warm water immersion (thermoneutral control) group. Specific methods for each group are described below.

#### Core body temperature measurement

3.4.1

Intestinal temperature is used to estimate body core temperature in all participants and measured via a telemetric pill BodyCAP USA (eCelcius). The pill travels through the gastrointestinal tract and transmits temperature to a receiving device outside of the subject’s body. Body core temperature may also be measured using an oral thermometer. The pill typically passes through an individual’s system within a few days. The pill is first administered upon arrival to the CTSU and 30 min prior to water immersion. Once core body temperature is detected, it is measured at 10 min intervals throughout the duration of the intervention.

Upon arriving at CTSU, study staff will check to see if core temperature senor is still reading from previous visit. If signal still present, no new sensor is provided. When no signal is present, a new sensor is ingested and the participant rests for 30 min. The signal is checked again prior to immersion. If the sensor has no or bad signal, oral temperature will be recorded during the visit.

#### Water immersion (heat therapy) group

3.4.2

Participants will be immersed up to the shoulder in a 40.5 °C water therapy bath until core body temperature (Tc) reaches 38.5 °C, ~30 min, as previously established with updates via personal communication (3). Participants will then remain in the water bath submerged to waist level to maintain core temperature between 38.5 and 39.0 °C for another 15 min (total of 45 min). Following heat therapy, Participants will exit the hot tub and be monitored for another 10 min, or until core temperature falls below 38.5 °C. Participants are asked to provide a urine sample to check urine specific gravity to confirm euhydration via urine specific gravity < 1.02 using a refractometer (Fisherbrand™ Handheld Analog Clinical Refractometer, Thermo Fisher Scientific, Waltham, MA). If urine specific gravity is > 1.02, subjects are asked to consume 5 mL kg − 1 of water prior to entering the hot tub (3).

Signs and symptoms of heat related illness are also continuously monitored by study staff. HR and BP measurements are taken every 10 min during the study visit. If heart rate increases > 60 beats/min above resting or increases > 20 beats/min within a 5 min time period, participants are moved to a seated position if they were previously fully submerged or removed from the hot tub if they were already sitting up. If body temperature reaches 39.5 °C or the participants experience symptoms of heat related illness, we will begin a Rapid Cooling Protocol: (1) Immediately remove subject from the hot tub; (2) Place ice packs in subject’s groin and axillae (armpits); (3) Mist subject constantly using a spray bottle filled with tepid (15 °C) water; (4) Place a large fan to circulate warm room air directly at the subject; (5) Continuously monitor body temperature, blood pressure, and heart rate for 20 min. Participants are encouraged to drink water ad libitum during the session. Body weight is measured using a scale before and immediately after all sessions. Participants that do not drink enough water to compensate for sweat loss (body weight loss > 1%) will drink additional fluids to make up this difference prior to leaving the study visit.

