#### Warm water immersion (thermoneutral control)

3.4.3

Because hydrostatic effects of water immersion may affect physiology, we include a comparison group comprised of individuals exposed to warm water immersion (thermoneutral condition). We follow procedures identical to the heat therapy protocol, except that the warm water therapy bath will be 36 °C. Prior work has shown that these conditions maintain core temperature within 0.2 °C of resting (3). This will ensure that both groups are exposed to conditions that are equivalent in terms of any hydrostatic effects, engagement, and patient experience.

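### The heart-rate trigger of more than 20 beats/min within 5 min cannot be applied directly or promptly from readings taken every 10 min

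*Protocol article*

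**What the plan says.** Section 3.4.2 (heat therapy group) sets the measurement schedule: "HR and BP measurements are taken every 10 min during the study visit". The next sentence sets the action rule: "If heart rate increases > 60 beats/min above resting or increases > 20 beats/min within a 5 min time period", then "participants are moved to a seated position if they were previously fully submerged or removed from the hot tub if they were already sitting up".

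Three other statements bear on what staff can see during immersion:

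- Section 3.4.2, continuous observation in the tub: "Signs and symptoms of heat related illness are also continuously monitored by study staff". Heart rate is not named there.
- Section 3.4.2, last step of the Rapid Cooling Protocol: "Continuously monitor body temperature, blood pressure, and heart rate for 20 min". This begins only after removal for temperature or symptoms.
- Section 3.4.1, core temperature: "Once core body temperature is detected, it is measured at 10 min intervals throughout the duration of the intervention". Section 3.8 adds that core temperature is monitored throughout therapy.

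For equipment, section 2 says "Heart rate and blood pressure will be captured with an automatic blood pressure monitor". Section 3.4.3 carries everything over to the control arm apart from the water temperature: "We follow procedures identical to the heat therapy protocol".

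**The concern.** The trigger has two limbs. The absolute limb (more than 60 beats/min above resting) can be checked at any single reading. The rate-of-rise limb needs two readings no more than 5 min apart, and the schedule never provides them. Staff following the text as printed cannot tell in time whether the rule has been met. For many rises they cannot tell even afterwards.

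Participants are 65 or older with metabolic impairment, and the hot arm is taken to a core temperature of 38.5 to 39.0 °C. A rise of 21 to 40 from near resting does not reach the absolute limb, so the rate-of-rise limb is the only heart-rate rule that covers it. The trigger also changes treatment, because it ends full submersion or takes the participant out of the tub. An unclear rule therefore invites different handling by different staff. With 30 hot-arm participants and up to 30 sessions each, it applies in up to 30 × 30 = 900 hot sessions, besides those in the control arm.

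**Working it through.** The document gives no figure to reproduce. The check compares the two stated intervals and then works out what 10-min readings can show.

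**Inputs (section 3.4.2):** reading interval 10 min; trigger window 5 min; trigger size more than 20 beats/min; immersion 45 min.

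**Step 1: what a net change between consecutive readings implies.** Split the 10 min into two 5-min halves.

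- Net rise above 40: the halves sum to more than 40, so at least one exceeds 20. The trigger was met, but this is known only at the later reading.
- Net rise above 20 and up to 40: undetermined. A steady rise of 30 is 15 per 5 min (not met); an abrupt rise of 30 is met.
- Net rise of 20 or less: does not exclude a rise above 20 that wholly or partly fell back.

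**Step 2: delay.** A steady rise of just over 4 beats/min each minute, starting at a reading, meets the trigger at 5 min (5 × 4 = 20) and is first visible at 10 min, so it is 5 min late. An abrupt rise just after a reading can wait almost 10 min.

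**Step 3: illustration.** Assumptions, not taken from the document: a linear rise of size R over 5 min, then a plateau; heart rate otherwise flat; start time uniform relative to the readings. Let T be the reading interval and c the net rise that must be exceeded between consecutive readings.

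- With probability (T − 5)/T the whole rise falls in one interval.
- Otherwise, with probability 5/T, a reading splits it into fractions u and 1 − u, with u uniform on 0 to 1. The larger part exceeds c with probability 2(1 − c/R), for c < R ≤ 2c.

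For c < R ≤ 2c, the share detected is (T − 5)/T + (5/T) × 2(1 − c/R). It is 0 for R ≤ c and 1 for R > 2c.

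- Trigger provable from 10-min readings (T = 10, c = 40): 0.5 + (1 − 40/R). For R = 45 this is 0.5 + 0.111 = 0.611.
- Rise above 20 seen with 5-min readings (T = 5, c = 20): 2(1 − 20/R). For R = 30 this is 2 × 0.333 = 0.667.
- Rise above 20 between 10-min readings (T = 10, c = 20): 0.5 + (1 − 20/R). For R = 25 this is 0.5 + 0.2 = 0.700.

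| Rise R (beats/min) | Provable, 10-min readings | Above 20, 5-min readings | Above 20, 10-min readings |
|---|---|---|---|
| 25 | 0 | 0.400 | 0.700 |
| 30 | 0 | 0.667 | 0.833 |
| 35 | 0 | 0.857 | 0.929 |
| 40 | 0 | 1.000 | 1.000 |
| 45 | 0.611 | 1.000 | 1.000 |
| 50 | 0.700 | 1.000 | 1.000 |
| 60 | 0.833 | 1.000 | 1.000 |

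Every rise in the table meets the trigger. The last column is not proof that the protocol's trigger was met, because a slower rise of the same size over 10 min looks identical.

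**Step 4: readings per session, timed from tub entry.** Every 10 min: 0, 10, 20, 30, 40, which is 5. Every 5 min: 0, 5, …, 45, which is 10. Difference: 5.

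**The case against.** The strongest reply is that the article condenses a fuller protocol and that the 10-min schedule may describe when heart rate and blood pressure are logged together, with heart rate watched in between. A rule written in 5-min terms fits that reading. So does the continuous heart-rate monitoring required during rapid cooling, which implies that the means exist. The reading is possible, but it is inference: the text says measurements are taken every 10 min and reserves continuous observation in the tub for signs and symptoms. The point is also not about missing detail, since the article states both an interval and a window and they do not fit together.

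Some further objections stand in part:

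- The blood pressure monitor in section 2 is described next to the glucose tolerance test. No section says which heart-rate device is used at the tub, so this does not show that only spot readings are available there.
- Other protections exist. Participants are lowered to waist level once core temperature reaches 38.5 °C, a continuing rise eventually reaches the absolute limb, and staff may repeat a reading. High-risk participants need physician clearance, a recent myocardial infarction or coronary symptoms exclude, and an external committee reviews adverse events every 6 months. These limit the consequence without making the trigger workable.
- The shares rest on a simple assumed rise. The document does not say how often such rises occur, so missed events cannot be counted.

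**Conclusion.** The concern holds. As printed, the rate-of-rise limb cannot be applied directly or promptly, because the reading interval is twice the trigger window. That conclusion needs no model. The size is illustrative and depends on the assumed 5-min rise and plateau: no rise of 21 to 40 is provable, and 61% to 83% of rises of 45 to 60 are, with a delay that can approach 10 min.

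This should be fixed, but it is a bounded safety-monitoring problem. Participants are not left unprotected, and the sample size and primary analysis are unaffected. If heart rate is in practice displayed continuously, saying so resolves the point.

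**What to change.** State in section 3.4.2 that heart rate is displayed continuously during immersion, or at minimum read every 5 min, in both arms. Blood pressure can stay at every 10 min. Continuous display is preferable, because a 5-min reading can still split a rise: under the same assumptions, a rise of 30 shows as above 20 in one interval for only about 67% of start times.

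The cost is a one-sentence correction, brief staff retraining, and either a pulse display usable at the tub or about 5 more heart-rate readings per session by staff already present.

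If only 10-min readings are feasible, restate the trigger as a rise of more than 20 beats/min between consecutive 10-min readings, for the safety physician to confirm. This makes the rule workable but is second best. It leaves a delay of up to almost 10 min and would miss about 30% of rises of 25 in the illustration (1 − 0.700). It also acts on slower rises (over 20/10 = 2 instead of over 20/5 = 4 beats/min each minute), so some participants would be moved or removed earlier and receive less heat. That loss would probably fall mainly on the hot arm and narrow the contrast under test.
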